## Abstract

**Background:** Early psychosocial interventions targeting cognitive and functional outcomes in individuals at clinical high risk for psychosis are a research priority. An even greater need is the identification of effective interventions in underserved populations. Compensatory Cognitive Training (CCT) is a psychosocial intervention with demonstrated efficacy in chronic schizophrenia and first episode psychosis, but remains to be evaluated in pre-illness phases. The aim of this study was to describe the development and implementation of an ongoing pilot randomized controlled trial investigating the efficacy of group-based, manualized CCT, as compared to recreational therapy (RT), for Latino participants at clinical high risk for psychosis (CHR) in both the United States and Mexico. It is hypothesized that, in comparison to those receiving RT, participants receiving CCT will show significant improvements in neurocognitive performance and functional capacity (co-primary outcomes) and self-rated functioning and clinical symptoms (secondary outcomes).

**Methods:** Latino CHR participants aged 12–30 years will be included in the study. Both CCT and RT will be delivered in either Spanish or English, depending on group preference. Additionally, all assessments will be administered in participants’ preferred language. A comprehensive assessment of neurocognitive and functional performance and clinical symptomatology will be performed at baseline, mid-intervention (4 weeks, 8 weeks), post-intervention (12 weeks) and 3-month follow-up. The primary outcome measures are neurocognition and functional capacity, as assessed by the MATRICS (Measurement and Treatment Research in Cognition in Schizophrenia) Consensus Cognitive Battery and the University of California, San Diego Performance-Based Skills Assessment-Brief, respectively. Furthermore, secondary outcomes measures will be used to examine change in clinical symptoms and self-reported functioning in response to CCT versus RT.

**Discussion:** The evaluation of a novel treatment such as CCT in CHR youth will provide empirical support for a low risk, comprehensive cognitive intervention that could have important implications for public health if it improves neurocognition and functioning.

## Introduction

Recent efforts to extend medical prevention models to the field of schizophrenia have resulted in systematic, reliable identification of individuals who are at clinical high risk (CHR) for imminent onset of psychosis (i.e., putative prodromal psychosis) (1, 2). Compared to psychotic disorders, the symptoms of psychosis-risk syndrome are less severe and more transient. Symptoms are not longstanding trait-pathology, but rather present as a marked change in individual’s mental state, evidenced through report from self and concerned others. Specific subtypes of the psychosis-risk syndrome are identified through formal structured clinical interview and are differentiated through individual risk factors. Broadly, risk factors for psychosis-risk syndrome include presence of: attenuated positive symptoms, negative symptoms, cognitive impairment or cognitive decline, decline in social, and/or role functioning, as well as family history of psychosis (3, 4). Diagnosis of a psychosis-risk syndrome requires that symptoms are associated with functional impairment and/or distress and of recent onset or worsening.

Findings from the North American Prodrome Longitudinal Study (NAPLS) have established that within the first 1–2 years after formal identification of being at CHR for psychosis, 20–40% of individuals go on to develop an acute psychotic illness (3, 5, 6). Despite advances in the early identification of individuals meeting CHR criteria, there is significant need for effective interventions that can be implemented early in the course of illness to improve symptoms and functional outcomes, especially considering that the strongest predictors of conversion to psychotic illness include modifiable risk factors such as prodromal symptom severity (as measured through structured interview), declines in social functioning, as well as verbal learning and memory deficits (6). Namely, there is a need for interventions that target the emerging neurocognitive (7–9), information processing (10–12), social, role, and global functioning deficits (13, 14) that characterize the prodromal period of illness. Not only are these early deficits disruptive to normal development and life trajectories, but they are also predictive of later conversion to psychotic illness (6, 15).

Antipsychotic medication, although effective in controlling positive symptoms, does not ameliorate cognitive deficits (16), nor has it shown any effects on conversion in randomized clinical trials (17, 18). Moreover, ethical concerns regarding exposing young people to psychotropic agents when less than half (~35%) are expected to convert to psychosis (19, 20) further support “staging” the prodromal period much like other medical illnesses (e.g., cancer, diabetes) and using less invasive treatments (psychosocial, education) for the early stages. Neurocognitive deficits are present across all identified stages of the CHR state and remain relatively stable, even during symptomatic remission upon illness onset (21). As such, an individualized, low risk treatment algorithm that focuses on neurocognition and functioning, in addition to the presenting subsyndromal psychotic symptoms, is a logical intervention strategy for this phase of the illness.

To date, there have been a limited number of randomized controlled trials analyzing the effectiveness of various psychosocial interventions in CHR, such as cognitive behavioral therapy (CBT), family focused therapy (FFT), or cognitive remediation (5, 22–24). Meta-analyses of psychosocial treatment effects on attenuated psychotic symptoms and negative symptoms yielded no statistically significant treatment effects for any intervention examined, although there were trends (p = .07) for CBT, FFT, and cognitive remediation (25, 26). Importantly, the existing RCTs use “transition to psychosis” as the primary outcome measure of treatment efficacy. However, the goal of psychosocial treatments may be reframed as improving cognitive, social, and functional impairments that are associated with poor prognosis in CHR, rather than preventing conversion to psychosis. In other words, for some individuals, “transition to psychosis” may be inevitable, but the degree of impairment associated with psychosis can be reduced if these individuals are provided skills to better cope with the cognitive and functional deficits associated with CHR.

In fact, cognitive deficits are a key determinant of functional outcomes in people with schizophrenia (27, 28) as well as individuals meeting CHR criteria (29, 30), irrespective of later development of a psychotic illness (15, 31, 32). Thus, there is a critical need for early interventions to improve cognitive impairment (and, therefore, everyday functioning) rather than focusing solely on symptomatic remission. Cognitive intervention trials (i.e., cognitive remediation or cognitive training) in individuals meeting CHR or early psychosis criteria remain limited and have produced mixed findings (33); although improvements in cognitive outcomes have been noted in some cognitive domains, these cognitive gains do not always generalize to improvements in community functioning. Although pro-cognitive interventions in pre- and early illness stages appear promising, preliminary evidence suggests that a compensatory strategy approach may best target areas of cognition typically impaired in early psychosis (34).

Compensatory Cognitive Training (CCT; (35–37), a strategy-based cognitive training approach, is one such psychosocial intervention that may hold promise as an efficacious treatment for CHR individuals. The most recent review and meta-analysis of cognitive remediation studies (35) found the largest effect sizes for compensatory strategy-based approaches in the context of psychiatric rehabilitation. In addition to improvements in neurocognitive performance and functional outcomes, CCT has demonstrated a large effect size for negative symptoms (38, 39). CCT strategies teach participants how to bypass their deficits and directly address functional recovery through a focus on application of appropriate cognitive strategies in the real world. In essence, CCT provides an intervention that targets healthy neural circuitry to compensate for damaged circuit elements, or even protect this circuitry from future damage (40). The merits of CCT also exist in its format; it is manualized, group-based, low-tech, brief (38), and can easily be applied in the community in English or Spanish, making it a practical intervention for underserved populations.

Latino CHR individuals represent an underserved population in the United States. Latinos have become the largest minority group in the US (41); more than half (~54%) of California’s elementary children are now of Latino origin (42). Despite the rising population of Latinos, disparities in mental health care continue to exist (43). Availability of and access to mental health resources is also limited in Mexico, with the Instituto Nacional de Neurología y Neurocirugía (INNN) serving as a local and national reference institution for the evaluation of CHR and early psychosis cases in Mexico City, a catchment area of over 20 million people. Latinos with CHR also present unique clinical challenges, presenting greater educational needs and exhibiting more severe negative symptoms predictive of conversion to psychosis (44).

Considering negative symptom severity is a predictor of long-term poor psychosocial functioning in schizophrenia (45) and CHR patients (30), and the lack of efficacy of any psychosocial or pharmacologic interventions in improving this symptom dimension in CHR patients (26), CCT’s demonstrated efficacy for improving both cognition and negative symptom severity makes it a suitable intervention to evaluate within Latino CHR youth. As such, the aim of this paper is to describe the development and implementation of an ongoing pilot randomized controlled trial investigating the efficacy of CCT, as compared to recreational therapy (RT), for CHR Latino participants in both the United States and Mexico. We hypothesize that, in comparison to those receiving RT, participants receiving CCT will show significant improvements in neurocognitive performance and functional capacity (co-primary outcomes) and self-rated functioning and clinical symptoms (secondary outcomes).

## Design and Methods

We are currently conducting a dual center (University of California, San Diego [UCSD] and INNN) randomized controlled trial of CCT compared to RT for CHR Latino youth in the United States and Mexico. The study is registered as a clinical trial (Clinical Trials registration number: NCT02245607). Baseline assessment confirms CHR criteria, and participants are subsequently randomized in groups to receive group-based CCT or RT. Study procedures were approved by the University of California, San Diego Institutional Review Board and by the Ethics and Scientific Committees of INNN.

### Participants

Projected enrollment is 120 CHR Latino youth (60 participants per site). In San Diego, participants are referred to the study by community health practitioners in San Diego who serve the Latino community, public schools in high Latino districts, County Mental Health, and the National Alliance on Mental Illness. In Mexico City, participants are recruited *via* the Neuropsychiatric Service, Early Psychosis Clinic, an advocacy group (Asociación de Familiares y Amigos de Personas con Esquizofrenia - AFAPE), and the Adolescent Study of Neuropsychiatric Assessment and Imaging (PIENSA) Program at INNN. Inclusion criteria are: 1) between the ages of 12 and 30; 2) meet CHR criteria per the Structured Interview for Prodromal Syndromes (SIPS); and 3) be of Latino descent. Specific to the Mexico City site, participants are eligible only if Spanish is their preferred language. Exclusionary criteria are: 1) current or lifetime psychotic disorder; 2) concomitant medical or neurological illness; 3) brain injury with loss of consciousness >30 min; 4) current substance abuse that interferes with group or assessment procedures or is judged to be causing subsyndromal psychotic symptoms (excluding nicotine); 5) IQ < 80; 6) high suicidal risk; and 7) Axis I disorder or substance use that better accounts for subsyndromal psychotic symptoms. Latino descent was identified through participant/family self-report. Only Spanish-speaking individuals were eligible for enrollment at the INNN site to reduce confounding factors associated with using two separate manuals presented in different languages for groups at that site. Psychotropic medication is permitted, including antipsychotics, antidepressants, and mood stabilizers. All cases are discussed in a weekly conference call between sites to reach consensus on inclusion/exclusion criteria and symptom and functional ratings. All participants over the age of 18 provide written informed consent; minors provide assent with written consent by a parent or legal guardian.

### Treatment

Eligible participants are assigned to one of the two treatment conditions: CCT and RT. Both treatments are manualized, 12-week interventions. Via a randomization schedule developed by the study statistician, all eligible participants are randomized in groups (goal 4–6 per group) to receive 12 weeks of CCT or RT. Moreover, participants’ age is factored in the randomization process to ensure that each intervention group only includes participants falling within a distinct age group (12–14, 15–17, and 18–30). This guideline was determined through direct communication with the National Institute of Mental Health (NIMH), given NIMH’s concern for minors being co-enrolled and randomized into the same group with legal-aged adults.

#### Compensatory Cognitive Training

CCT is delivered in accordance with the manual and has been described extensively elsewhere (38). Briefly, participants in the CCT group receive weekly 90-min group CCT sessions for 12 weeks, which involve education regarding targeted skill areas as well as modules of compensatory strategies targeting prospective memory, attention, learning/memory, and executive functioning. The CCT strategies are presented in an interactive, game-like format to maintain interest and reduce attrition. Homework assignments are designed to encourage additional practice outside treatment sessions. At the beginning of each session, previous homework assignments are reviewed or completed *in vivo* to ensure skill proficiency and execution. As the ongoing study is a feasibility trial, minor age-related modifications were made as necessary to ensure CCT was engaging and relevant to the speciﬁc needs of young Latinos with CHR (e.g., using Spanish names, focusing on school-related versus work-related examples).

English and Spanish versions are used in the study and employed based on the group’s preferred language. The Spanish translation of the CCT manual (46), a collaborative effort between investigators at UCSD, INNN, and the University of Deusto, Bilbao, is applicable in both Spain and Latin America (translation performed by natives of Spain and Mexico). Translation back to English by translators unfamiliar with the manual was very successful and the final Spanish CCT manual required very little modification.

#### Recreational Therapy

RT was selected as a robust control condition, a group therapy intervention that provides the same frequency and amount of therapist and other group member contact as CCT, but does not provide any cognitive training. Participants assigned to the RT sessions participate in different recreational activities targeting their popular culture awareness, art, and physical activities. The 12 sessions of RT, also broken down into modules, consist of discussions on topics such as music, current events, art, and health. Reference materials were selected from current media (newspapers, magazines, and internet). Practice of RT skills is encouraged outside of session, but no formal homework assignments are given. At the beginning of each session, previous week’s concepts are reviewed. The purpose of these sessions is to provide participants with access to information that would encourage social interactions and the addition of physical activity to their daily routine.

### Assessments

Following enrollment/randomization, participants complete assessments at baseline, mid-intervention (4 weeks, 8 weeks), post-intervention (12 weeks) and 3-month follow-up, conducted by clinical raters and research assistants blind to group assignment (see **Table 1** for the Assessment Overview). Participants are compensated for their time per assessment and at each group session to offset the cost of transportation. Following baseline assessment, participants receive 12 weeks of their assigned intervention, delivered by bachelor’s level or above therapists at each site. Therapists administer both treatments in an alternating schedule to avoid therapist effects in the design. The primary outcome measures are neurocognition and functional capacity, as assessed by the measures detailed below. Furthermore, secondary outcomes measures will be used to examine change in clinical symptoms and self-reported functioning in response to CCT versus RT.

**Table 1 T1:** Assessment Overview.

	Time (Hour : Min)	Baseline	Week 4	Week 8	Week 12	Week 24
**Clinical (Day 1)**	**2:30**	**X**			**X**	**X**
Demographics	:15	**X**			**X**	**X**
SCID-I	1:00	**X**			**X**	**X**
SIPS/SOPS	1:00	**X**	**X**	**X**	**X**	**X**
AUS/DUS	:15	**X**	**X**	**X**	**X**	**X**
**Functional (Day 1)**	**1:35**	**X**			**X**	**X**
SAS-SR	:15	**X**			**X**	**X**
GAF	:05	**X**			**X**	**X**
SLoF	:30	**X**			**X**	**X**
UPSA	:45	**X**			**X**	**X**
***Day 1 Total***	***4:05***	**X**			**X**	**X**

**Neurocognitive** **Battery (Day 2)**	**2:15**	**X**			**X**	**X**
**General Intelligence**						
WAIS Vocabulary	:15	**X**			**X**	**X**
WAIS Block Design	:10	**X**			**X**	**X**
**Verbal Learning**						
HVLT	:05	**X**			**X**	**X**
BVMT	:05	**X**			**X**	**X**
**Processing Speed**						
BACS Symbol Coding	:05	**X**			**X**	**X**
Category Fluency	:05	**X**			**X**	**X**
Trails A	:05	**X**			**X**	**X**
**Attention/Vigilance**						
CPT-IP	:10	**X**			**X**	**X**
**Working Memory**						
WMS III Spatial Span	:10	**X**			**X**	**X**
LNS	:10	**X**			**X**	**X**
**Executive Functioning**						
NAB Mazes	:10	**X**			**X**	**X**
WCST	:10	**X**			**X**	**X**
***Day 2 Total***	***2:15***	**X**			**X**	**X**

***Exit Interview***	***:30***				**X**	
**Total Assessment Time** (H:M)		**6:20**	**1:15**	**1:15**	**6:50**	**6:20**

Structured Interview for Prodromal Syndromes (SIPS), Scale of Prodromal Symptoms (SOPS), Structured Clinical Interview for DSM-IV (SCID) Axis I, The Social Adjustment Scale – Self-Report (SAS-SR), Global Assessment of Functioning (GAF), Specific Level of Functioning (SLoF), The UCSD Performance-Based Skills Assessment (UPSA), Wechsler Adult Intelligence Scale (WAIS), Hopkins Verbal Learning Test (HVLT), Brief Visual Memory Test–R (BVMT), Brief Assessment of Cognition in Schizophrenia (BACS), Category Fluency, Trail Making Part A, Continuous Performance Task Identical Pairs (CPT-IP), Wechsler Memory Scale (WMS), Univ. of Maryland Letter-Number Span (LNS), Neuropsychological Assessment Battery (NAB) Mazes, Wisconsin Card Sorting Test (WCST).

#### Cognitive and Functional Assessment

Premorbid intellectual functioning is assessed *via* the Wechsler Adult Intelligence Scale (WAIS), Block Design and Vocabulary subtests. Participants are administered an expanded MATRICS (Measurement and Treatment Research in Cognition in Schizophrenia) Consensus Cognitive Battery (MCCB) in English or Spanish (47). The MCCB has excellent qualities, including psychometric properties for longitudinal studies, utility as a repeated measure, relevance to functional outcome, brevity, ease of use, and participant tolerability. These tests are administered according to published standardized procedures. As part of collaborative studies, the UCSD team has traveled to Mexico City and standardized administration of the neuropsychological battery. The battery includes the following domains: 1) Estimated IQ: Wechsler Adult Intelligence Scale Vocabulary and Block Design, 2) Learning & Memory: Hopkins Verbal Learning Test, Brief Visual Memory Test–R, 3) Processing Speed: Brief Assessment of Cognition in Schizophrenia: Symbol Coding, Category Fluency, Trail Making Part A, 4) Attention/Vigilance: Continuous Performance Task Identical Pairs, 5) Working Memory: WMS III Spatial Span, University of Maryland Letter-Number Span, and 6) Executive Functioning: Neuropsychological Assessment Battery Mazes, Wisconsin Card Sorting Test. A Global Cognitive Index will combine z scores of all cognitive domains per established methods (8). The University of California, San Diego Performance-Based Skills Assessment-Brief (UPSA-Brief) was selected to measure performance-based functional capacity (48), along with UPSA-Child and Adolescent version for adolescents. The Specific Levels of Functioning (SLOF) scale is used as a self-reported functioning measure because of its concordance with objective ability measures (49). In addition, the modified Global Assessment of Functioning (50) and the Social Adjustment Scale (51) are administered.

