### Data Analysis

The purpose of this pilot RCT is to examine feasibility and generate effect sizes to establish benchmarks for future studies, not to complete an adequately powered efficacy study. Power calculations based on Cohen method (63) and the method provided by Hedeker et al. for the Random Regression Model (64) indicated that with the proposed sample size, we will have a minimum 80% power to detect a medium to large effect across groups, consistent with the medium to large effects in prior studies.

A linear mixed model, with post-hoc procedures if indicated, will be used to analyze data in order to compare CCT versus RT in Latino CHR subjects in the United States and Mexico (co-primary outcomes: neurocognition [Global Cognitive Index and individual domain scores] and functional capacity; secondary outcomes: self-reported functioning and clinical symptom severity). Feasibility data such as recruitment rate, consent rate, reasons for not participating, reasons for dropping out, participants’ satisfaction, and their suggestions to improve the study will be tabulated and will be analyzed descriptively.

Furthermore, predictors (moderators) of response to CCT versus RT, including age, baseline symptom severity, neurocognition, and comorbidity, will be explored. Moderators will be examined by building hierarchical linear models with potential moderator variables (e.g., baseline symptoms, neurocognition, functioning, age, and comorbidity) included in the model (65). The linear model to be used for both moderator and mediator analyses will compare CCT versus RT treatment groups. The independent variables are treatment group, moderator, and the treatment-moderator interaction. An interactive effect will mean that the effect of treatment on individual subjects depends on their value of moderator.

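### As written, the co-primary Global Cognitive Index includes Estimated IQ, which the protocol itself calls premorbid, and this may dilute the treatment effect

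*Protocol article*

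**What the plan says.** All references are to the protocol article.

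- **Cognitive and Functional Assessment, opening:** "Premorbid intellectual functioning is assessed" with the WAIS Block Design and Vocabulary subtests.
- **Same section, domain list:** "The battery includes the following domains: 1) Estimated IQ: Wechsler Adult Intelligence Scale Vocabulary and Block Design". Five more numbered domains follow: learning and memory, processing speed, attention/vigilance, working memory, and executive functioning.
- **Same section, index rule:** "A Global Cognitive Index will combine z scores of all cognitive domains per established methods (8". No weights and no exceptions are given, and the construction is deferred to a cited source.
- **Table 1:** the rows for "WAIS Vocabulary" and Block Design sit in the neurocognitive battery and are marked at baseline, week 12 and week 24, on the same schedule as the outcome tests.
- **Compensatory Cognitive Training:** the sessions contain "modules of compensatory strategies targeting prospective memory, attention, learning/memory, and executive functioning". General intelligence is not mentioned here, nor as a CCT target under Design Considerations.
- **Data Analysis:** "co-primary outcomes: neurocognition [Global Cognitive Index and individual domain scores] and functional capacity". Change in the index is also the proposed mediator of the effect on functional capacity.

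**The concern.** The same two subtests have two roles that do not fit together. They are described as measuring a level that precedes the risk state, and they are also counted among the domains that make up an outcome of a 12-week intervention. Premorbid ability is not something that strategy training is meant to move.

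Estimated IQ then enters the analysis in three places: inside the composite, as a co-primary domain score of its own, and inside the change score used for mediation.

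The effect size is what is mainly at stake. The article describes the trial as a pilot whose main product, besides feasibility data, is effect sizes on which later studies can be planned. A composite with a component that is not expected to respond may give a smaller benchmark than the trainable domains would. A composite whose content is unclear gives a benchmark that later trialists cannot interpret.

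**Working it through.** **Inputs from the article.** Six listed domains, with Estimated IQ the first. "Projected enrollment is 120 CHR Latino youth (60 participants per site", that is 120 in total. Power of at least 80% for a medium-to-large effect, with no numeric effect size.

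**Assumed, because not stated.** 1:1 allocation (60 per arm), two-sided alpha 0.05, equal domain weights, and d = 0.5 for medium and 0.8 for large. Dropout and the grouping of participants are ignored, so the absolute powers serve only to compare the two index definitions.

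**Step 1: the plan's own figure.** Power = Φ(d·√(n/2) − 1.960).
- d = 0.5, n = 60: 78.2% (77.5% with the t distribution).
- d = 0.8, n = 60: 99.2%.
- Smallest d with 80% power: (1.960 + 0.842)·√(2/60) = 0.511.

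The stated 80% is thus reproduced for a medium or larger effect. In Step 3 the five-domain index is given d = 0.512 (power 80.1%), which sits at the edge of that claim.

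**Step 2: effect in z units.** Let each of the other five domains shift by δ and Estimated IQ by f·δ. The six-domain mean shifts by (5 + f)δ/6. With f = 0 this is 5/6 of δ, a fall of one-sixth (16.7%).

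**Step 3: standardised effect.** Let ρ be the correlation among the five domains, r their correlation with Estimated IQ, and v the SD of the IQ score (or IQ change) relative to the others. The six-domain effect as a fraction of the five-domain effect, with f = 0, is

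ratio = √[(5 + 20ρ) / (5 + 20ρ + v² + 10rv)].

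The article gives none of ρ, r or v, so a range is shown, with ρ from 0 to 0.7. For example, ρ = r = 0.3 and v = 1 gives √(11/15) = 0.856.

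| IQ variability v | Correlation r | Ratio | Power at 60 per arm | n per arm for 80% |
|---|---|---|---|---|
| 0 (IQ hardly changes) | any | 1.00 | 80% | 60 |
| 0.5 | 0 | 0.98 to 0.99 | 78% to 80% | 61 to 63 |
| 0.5 | equal to ρ (0.1 to 0.7) | 0.95 to 0.91 | 76% to 73% | 67 to 72 |
| 1 | 0 | 0.91 to 0.98 | 73% to 78% | 72 to 64 |
| 1 | equal to ρ (0.1 to 0.7) | 0.88 to 0.84 | 70% to 65% | 77 to 86 |

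**Step 4: if Estimated IQ does respond** (ρ = r = 0.3, v = 1). Multiply the ratio by (5 + f)/5.
- Half response: 1.1 × 0.856 = 0.94.
- Full response: 1.2 × 0.856 = 1.03, so no dilution.

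**Step 5: at a large effect.** Even the lowest ratio gives d = 0.8 × 0.839 = 0.671. Power is then Φ(0.671 × √30 − 1.960) = Φ(1.716), about 96%.

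**The case against.** **Inclusion is not proven.** The article says that domain scores are combined, not averaged, and points to a source that is not at hand and may leave IQ out. The abstract names the MATRICS battery as the neurocognitive measure, and the WAIS subtests are introduced separately from it. This stands as a caution. But the section goes on to describe an expanded battery, numbers Estimated IQ as its first domain, and puts every domain in the index. If IQ is left out, that sentence is misworded and still needs correcting.

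**Dilution is not certain.** This stands. The fall of one-sixth needs equal weights and no IQ response. A truly stable trait adds little variance to change, and the power loss then tends to nil. Nor is a six-domain index biased in the strict sense: it estimates its own quantity correctly, but that quantity is less useful.

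**Targets.** One might infer that only what CCT targets belongs in the index. Processing speed and working memory are not named targets either, so that argument would remove them too. What sets Estimated IQ apart is the protocol's own premorbid label.

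**Eligibility.** A reader might infer that these subtests also decide the IQ below 80 exclusion, which would make the component range-restricted by selection. They are the only IQ measure listed, but the Participants section names no instrument, so the documents do not support this.

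**Consequence.** The trial is a declared pilot, and the separate domain scores would show an effect in any single domain undiluted. This limits the harm but leaves the composite benchmark unclear.

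**Conclusion.** The point holds as an internal inconsistency in a co-primary endpoint: read literally, a measure labelled premorbid is part of the outcome. Confidence in the inconsistency is high; confidence in the size of its effect is moderate at most.

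With equal weights and an unresponsive Estimated IQ, the effect in z units falls by one-sixth. The standardised effect falls by 0% to about 16%, and 80% power becomes something between 80% and 65%. The lower end needs IQ change to be as variable as change in the other domains and strongly correlated with it, which fits a stable trait poorly.

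It would go too far to say that the stated power is wrong or that the effect is certainly attenuated. The stated 80% is reproducible under ordinary assumptions, and the trial does not claim to be an adequately powered test of efficacy. The main cost is a benchmark effect size that may be too small and is hard to interpret.

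**What to change.** 1. Define the Global Cognitive Index on domains 2 to 6: learning and memory, processing speed, attention/vigilance, working memory, and executive functioning. State the weights.
2. Remove Estimated IQ from the co-primary individual domain scores.
3. Use baseline Estimated IQ only as a descriptor or covariate.
4. Use the same five-domain index in the mediation analysis.
5. Report the six-domain version as a sensitivity analysis.

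If the investigators want to keep Estimated IQ in the index, they should say so and explain why a measure described as premorbid is expected to respond.

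The cost is about one sentence in the endpoint definition. All the tests are already collected. The change should be documented before any comparison by arm is seen. The downside is less comparability with earlier work that used an index including IQ, which the sensitivity analysis largely covers.
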